### Data entry and checks

Data will be entered into the secure electronic case report form (ALEA) and data validation will take place according to the procedures set out in the data management plan and data validation plan, both developed apriori. Missing data will be assessed to identify any specific challenges with any items of data collected. Missing data level is expected to be less than 20%. Data loss and mortality will inform number of participants needed to design a larger RCT. As this is a feasibility study data imputation will not be undertaken. Prior to statistical analysis, variables will be checked for missing and impossible and improbable values as defined by clinical opinion. Questions regarding the data will be directed to the data manager.

### Sample size calculation

This is a feasibility study, the results of which will be used to power a definitive study if appropriate; as such, no formal sample size calculation for effectiveness of the intervention has been undertaken. Ninety patients will be recruited, aiming for 30–45 participants at each site. We anticipate a 30% in hospital mortality /loss to follow-up with an estimate of 60 patients completing the study. This sample size of 90 will allow the estimate of recruitment rate to be made with a 95% CI of ±5.2% if the rate is observed to be around 30%, and with a CI of ±7.3% if the recruitment rate is observed to be around 50%. In addition, the sample of 90 recruited patients will allow the estimate of the mortality rate to be made with a 95% CI of ±9.5%, assuming the mortality rate was around 30%. Finally, assuming the recruitment rate was around 30%, a sample of 300 patients approached to take part in the study, leading to 90 enrolled patients would allow for the recruitment rate to be estimated with a 95% CI of ±5.2%. If the recruitment rate was nearer 50%, with 180 patients approached to recruit the 90 enrolled patients, the recruitment rate would be estimated with a 95% CI of ±7.3%.

### Statistical analysis

The analysis will be reported in line with the feasibility studies extension to the Consolidated Standards of Reporting Trials statement.^76^ The aims of the study were to estimate the recruitment, compliance and retention rates to inform the design of a future study and is not powered for hypothesis testing regarding the effectiveness of the intervention. Feasibility outcomes (recruitment, compliance and retention rates) will be presented with 95% CIs across the whole study population. Compliance and retention rates will also be presented by treatment arm to ensure balanced recruitment, but no formal statistical comparison tests will be made. Mortality and participant dropout rates will be presented with 95% CIs across the whole study population and within treatment arm. Clinical outcome data (secondary outcomes) will be presented as summary statistics using means and SDs or medians and ranges/IQRs, as applicable, across the whole study population and by treatment arm. These data will be used to inform the future trial but will not be used to draw conclusions about the effectiveness of the protocolised early rehabilitation intervention within this study.

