## Methods and analysis

### Study design

This is a two-centre feasibility study using a two-arm RCT, randomised 1:1, with blinded outcome assessments at ICU discharge, hospital discharge and 3-month follow-up. Patients will be recruited from two general ICUs, located in the south of the UK. They will not be recruited from our ICU on account that the intervention is now standard practice at this site. Prior to each site opening to recruitment, an audit of current physiotherapy practice will be undertaken over a 4-week period to evaluate what constitutes ‘usual care’ in each institution.

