### Primary outcome: feasibility to deliver the protocol as designed

Feasibility will be determined by measures of the recruitment process, intervention fidelity and outcome measurement completeness, specifically,

Study accrual rates: a minimum of 30% of eligible patients or one to two patients per site per month are enrolled.Protocol adherence: 75% of patients commencing intervention within 72 hours of ICU admission, minimum of 70% of planned interventions delivered.Blinded outcome assessment: functional assessment performed at three time points in 80% of survivors by physiotherapists working within the hospital but not within the ICU.

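### The planned compliance rate and its 95% CI are pooled over both arms, although the adherence criterion concerns only patients randomised to the protocolised arm

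*Protocol article*

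**What the plan says.** Adherence is the second of the three primary feasibility criteria. The section on the primary outcome words it as "Protocol adherence: 75% of patients commencing intervention within 72 hours of ICU admission, minimum of 70% of planned interventions delivered", and Objectives has the same thresholds. Neither place says which patients form the denominator.

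The Statistical analysis section then fixes the population for the estimate: "Feasibility outcomes (recruitment, compliance and retention rates) will be presented with 95% CIs across the whole study population". It continues: "Compliance and retention rates will also be presented by treatment arm to ensure balanced recruitment, but no formal statistical comparison tests will be made". The sentence after that treats two other rates differently: "Mortality and participant dropout rates will be presented with 95% CIs across the whole study population and within treatment arm".

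On design, the article says "This is a two-centre feasibility study using a two-arm RCT, randomised 1:1", and on size, "Ninety patients will be recruited, aiming for 30–45 participants at each site". Under Interventions and Group 2, the 72-hour start and the two additional sessions belong to the protocolised arm. Under Group 1, usual-care physiotherapy starts according to each hospital's own pathway. It has no 72-hour target and no planned number of sessions.

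**The concern.** The criterion measures something that half of the randomised patients are not meant to receive. A control patient has no study programme to start and no planned study sessions, yet the analysis text puts that patient into the population over which compliance and its interval are computed. What the pooled figure means then depends on how controls are scored, and the article does not say.

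The by-arm sentence repairs this only in part. It promises the by-arm rates but no interval for them, whereas mortality and dropout get intervals within arm. Its stated purpose, balanced recruitment, is not something that compliance or retention rates can show.

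At stake is the reading of one of three primary criteria. Under Implementation evaluation the feasibility outcomes are to be used to power the larger trial, so a diluted or inflated adherence rate could carry into its design.

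**Working it through.** **Inputs.** Total 90 (Sample size calculation). Allocation 1:1 (Study design), hence 90/2 = 45 per arm; the article does not print 45. Thresholds of 75% and 70% (Primary outcome).

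**1. The plan's own precision figures.** The Wald half-width is 1.96 × √(p(1−p)/n).
- Recruitment 30% of 300 approached: 1.96 × √(0.30 × 0.70/300) = 5.2 points (printed ±5.2%).
- Recruitment 50% of 180 approached: 1.96 × √(0.50 × 0.50/180) = 7.3 points (printed ±7.3%).
- Mortality 30% of 90: 1.96 × √(0.30 × 0.70/90) = 9.5 points (printed ±9.5%).

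All three reproduce. None of them concerns compliance, for which no precision is printed.

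**2. What a pooled start rate shows.** Let a be the on-time rate in the protocolised arm and c the share of controls scored as compliant. Then pooled = (45a + 45c)/90 = (a + c)/2.

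| Scoring of controls | Pooled rate when a = 75% | a needed for pooled 75% |
|---|---|---|
| None compliant (c = 0) | 37.5% | 150%, impossible; the maximum is 45/90 = 50% |
| All compliant (c = 1) | 87.5% | 50% |

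If the pooled rate were compared with 75%, c = 0 would give the wrong reading whenever the protocolised arm truly reaches 75%. With c = 1 the reading would be wrong whenever that arm lies from 50% up to just below 75%.

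**3. The share of planned interventions.** A control patient has zero planned study sessions. Counted by session, controls add nothing to numerator or denominator. Counted by patient, their share is 0/0. Either way the pooled population adds no information.

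**4. Precision when the protocolised arm is at 75%.**
- Within the arm, n = 45: 1.96 × √(0.75 × 0.25/45) = 12.7 points.
- Pooled with c = 0, rate 37.5%, n = 90: 1.96 × √(0.375 × 0.625/90) = 10.0 points.
- Pooled with c = 1, rate 87.5%, n = 90: 1.96 × √(0.875 × 0.125/90) = 6.8 points.

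Both pooled intervals are narrower than the one that answers the question, and both are centred in the wrong place.

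**5. A result that just passes.** 34 of 45 is 75.6%, with an exact (Clopper-Pearson) 95% CI of 60.5% to 87.1%. The same 34 over all 90 is 37.8%, with an exact CI of 27.8% to 48.6%.

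**The case against.** A reader might infer that the 75% criterion cannot be met as written. The documents do not support that. Objectives and Primary outcome speak only of patients, and since Interventions places the 72-hour start in the intervention arm, the natural reading is patients allocated to it. The analysis section describes how rates are presented and nowhere says that the pooled rate decides the criterion. The 50% cap applies only if someone uses the pooled rate that way.

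A reader might also infer that a printed adherence precision rests on the wrong sample size. No such figure is printed; the criticism applies only to the planned whole-population interval.

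It can further be said that compliance is undefined and might mean adherence to allocated care in both arms, since usual-care physiotherapists are asked whether they delivered study interventions. That is possible, but it leads to the c = 1 row above, which is no better for judging the threshold.

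Finally, a condensed article may leave definitions to the full protocol or analysis plan, and the results are descriptive. This fairly covers the interval method, including any allowance for repeated sessions within a patient, and no fault is found there. It does not cover the population, because the article states one and it does not fit the criterion. The by-arm rate does protect the point estimate, and that part of the defence stands.

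**Conclusion.** The stated population for the compliance estimate and its interval does not match the adherence criterion. The pooled rate is uninformative for the 75% threshold under either scoring of controls: 37.5% or 87.5% when the arm that matters is at 75%. The right point estimate will be available from the by-arm display, but without a stated interval and under a rationale that does not fit. At 75% that interval would be about ±12.7 points, so a result that just passes is compatible with about 60%.

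This is an error in stated wording with a simple correction. It does not show that the criterion is unattainable. The figures assume exactly 45 patients per arm and, for the two scorings, that either no controls or all controls count as compliant. Any share in between gives a pooled rate between the two values shown.

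**What to change.** - In Primary outcome, and likewise in Objectives, state that both adherence criteria are judged in all patients randomised to the protocolised arm.
- In Statistical analysis, give both adherence rates with a 95% CI within that arm, and note the expected precision for on-time start: about ±12.7 points at 75% with 45 patients.
- Keep whole-population estimates for recruitment and retention.
- Replace the balanced-recruitment reason for the by-arm display with one that fits, such as describing adherence in the protocolised arm and retention in each arm.
- Report any receipt of study interventions by control patients separately, as contamination, and do not merge it into a compliance rate.

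The cost is a few sentences. The adherence interval will be wider than a pooled one would suggest. No new data are needed.

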### Trial management

The chief investigator will ensure all study personnel are appropriately orientated and trained, oversee recruitment and report to the trial safety monitoring committee. Training will occur across sites using competency-based training developed at the primary site (University Hospital Southampton NHS Foundation Trust). A study steering group, consisting of an independent chair, expert members and two lay advisors will meet every 3 months. Fortnightly teleconferences with trial sites will be held to monitor conduct and progress. Timing and intervals of visits and teleconferences will be reviewed at 3 months to ensure optimal time use.

The chief investigator and principal investigators will facilitate local monitoring by the research and development quality manager, research ethics committee (REC) review and provide access to source data as required. A monitoring report will be produced, summarising the visit, documents and findings. The chief investigator will ensure that all findings are addressed appropriately. The steering group will review all events in a timely manner. Additional monitoring will be scheduled where there is evidence or suspicion of non-compliance with the study protocol.

A data management and safety committee will be chaired by an independent expert. Quarterly reports will be given to the committee once recruitment has commenced.

### Patient and public involvement

The study has been supported by patient advisory representatives. These representatives are members of the trial steering committee. Patient advisors partnered with us for the design of the study, the informational material to support the intervention, the burden of the intervention from the patient’s perspective and contributed to the dissemination plan

### Ethics and dissemination

Ethical approval has been granted by South Central Hampshire A Research Ethics Committee (REC reference 19/SC/0016). This study entitled: A feasibility study of Early Mobilisation Programmes in Critical Care (EMPRESS) was registered with Clinical Ttrials.gov on 10 December 2018.

Results of this proposed feasibility study will be disseminated for four key audiences: (1) patients and public; (2) intensive care staff, healthcare workers and potential future research delivery partners; (3) service delivery organisations; and (4) academic and potential future research collaborators. Dissemination activities will include feedback to patients and public involvement study focus group, feedback to study participants, presentations to local clinical teams and managers and commissioners and presentation at conferences attended by appropriate healthcare professionals. Where appropriate, results will be published in peer reviewed journals.

### Safety and adverse events

Early mobility within ICUs is safe. In a review of physiotherapy in a critical care rehabilitation programme, 1110 patients underwent 5267 rehabilitation sessions; physiological abnormalities or potential adverse events occurred in only 6 per 1000 interventions.^77^ Mobilisation interventions will only be delivered if patients fit the safety criteria defined in table 1. Similar safety criteria have been used in other ICU rehabilitation studies.^78 79^

All adverse events will be documented. Any intervention will cease according to stopping criteria detailed in table 1. Any such event will be recorded as an adverse event. The chief investigator will provide a monthly update to the safety monitoring committee. Serious adverse events are events that result in death, are life-threatening or require prolonged hospitalisation. Any such event will be reported in accordance with the NHS Health Research Authority guidance.

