### Group 1: usual care control group

In this pragmatic study, physiotherapy interventions will be guided by individual assessment and start in accordance with the usual care pathway within each institution. The focus of each session may be respiratory support, mobilisation or a combination of both. Interventions delivered will be determined by the physiotherapist in conjunction with the attending physician. Interventions include, where appropriate, passive or active range of movement, positioning and respiratory physiotherapy, and when able, sitting on the edge of the bed, standing (assisted or unassisted), standing to transfer to chair, marching on the spot and walking (figure 3). Usual interventions may occur at any time of day.

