### Group 2: Protocolised rehabilitation pathway

Patients will have usual care physiotherapy, in addition to the two protocolised intervention within 72 hours of ICU admission or as soon as possible thereafter. Patients will be screened for safety criteria to withhold the intervention prior to each planned intervention session (table 1).

**Table 1 T1:** Safety criteria for delivery of physical therapy interventions

	Criteria to commence physiotherapy	Criteria to stop/withhold physiotherapy intervention
Blood pressure	Mean Arterial Blood Pressure (MAP) 60–100 mm Hg, no change in vasopressor dose requirement for preceding 2 hours	Catecholamine-resistant hypotension with MAP <60 mm Hg
Heart rate	Between 40 and 140 beats/min	<50 or >140 beats/min
Respiratory rate	Sustained <40 breaths/min	Sustained >40 breaths/min
Temperature		>40°C
Oxygen requirement	If Fraction inspired oxygen (FiO_2_)>0.8 for passive exercise only	
	FiO_2_ <0.8 and (Positive End Expiratory Pressure) PEEP <15 cmH_2_O	
Desaturation		Sats fall <85% for>1 min
Other		Fall. Unplanned extubation. Acute bleeding. New-onset arrhythmia. Signs/symptoms of acute myocardial ischaemia. Patient pain/distress. Clinical team decides therapy intervention not appropriate. Refusal by patient or representative.

Those meeting criteria to withhold interventions will have issues addressed and reassessed for interventions 2 hours later. The two additional rehabilitation sessions will be delivered by the research physiotherapy staff including a therapy technician. This will comprise two mobility sessions the modality of the first, chosen at the discretion of the physiotherapist. The second session will be 30 min of supine cycling delivered in the afternoon.

The first rehabilitation intervention each day will be delivered in the morning. Planned interventions include passive or active range of movements, passive cycling, active cycling, in-bed exercises, sitting, mobilisation out of bed and walking. Daily assessment of the patient will be made to ensure the highest level of activity possible is provided for each individual patient given safety considerations and capability of the patient.

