The second session will be cycling based. An in-bed supine cycle ergometer (MotoMed Letto 2) will be used to engage the participant in passive, assisted or active cycling, or a combination, depending on the degree of patient cooperation (figure 3). The aim was for the patient to have 30 min of cycling per day, following a standardised cycling programme. If cycling is in passive mode, patients will commence cycling at 5 revolutions per minute (RPM), building up to 20 RPM over 5 min and continue this for 20 min before 5 min 5 RPM cool down. In the assisted or active mode, after the 5 min warm-up, cycling will continue for 20 min at patient-selected RPM followed by a 5 min cool-down at 5 RPM. In-bed cycling sessions will stop when the patient is deemed to be able to stand and transfer from bed to chair for both mobility sessions for two consecutive days. If patients are considered unable to have concurrent mobility therapy and respiratory weaning, mobility therapy will take priority, in agreement with the senior clinical team. Individual participants will receive the trial intervention on 5 days/week (Monday–Friday) for the duration of their ICU stay or a maximum of 28 days, whichever comes first. Patients will be monitored for cardiovascular and respiratory stability and safety of indwelling lines, tubes and catheters with predetermined criteria for termination of any session (table 1). Deviations from the planned protocol will be reported to determine potential barriers to implementation. Patients will be able to decline any intervention or outcome assessment at any time without compromise to their care.

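### As written, a session stopped by patient refusal or by clinical-team decision is recorded as an adverse event, so the safety count mixes non-safety stops with true safety events

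*Protocol article*

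**What the plan says.** The recording rule is in the protocol article under Safety and adverse events: "Any intervention will cease according to stopping criteria detailed in table 1. Any such event will be recorded as an adverse event". It points to Table 1, in the section on the protocolised pathway (Group 2), where a single column is headed "Criteria to stop/withhold physiotherapy intervention". That column holds blood pressure, heart rate, respiratory rate, temperature and desaturation limits, then events such as a fall, unplanned extubation, bleeding or a new arrhythmia. It ends with "Clinical team decides therapy intervention not appropriate. Refusal by patient or representative".

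Table 1 is put to use in the Group 2 section, first for screening ("Patients will be screened for safety criteria to withhold the intervention prior to each planned intervention session (table 1") and then for ending a session ("with predetermined criteria for termination of any session (table 1"). The same section lets patients decline any intervention without effect on their care, and has protocol deviations reported. The Discussion adds that reasons for not delivering protocol interventions will be collected, and that safety is among the things the study evaluates. The safety section provides for a monthly update to the safety monitoring committee.

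For usual care, the Group 1 section says only that "physiotherapy interventions will be guided by individual assessment and start in accordance with the usual care pathway within each institution"; it does not mention Table 1.

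**The concern.** A refusal, or a judgement that a session is unsuitable, is a reason why therapy was not given or not completed. It is not in itself harm to the patient, and the article elsewhere treats declining as a permitted choice. The recording rule nevertheless takes in everything in the Table 1 column, so these two items become adverse events alongside extubations and arrhythmias.

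At stake is the meaning of the descriptive safety count. A committee reading a monthly total could not tell from it how many patients came to harm and how many asked to stop. A team planning the definitive trial would take forward an event rate that depends partly on how willing patients and staff were to continue. In a study of 90 patients, where true safety events may be few, a modest number of such stops could make up much of the total.

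**Working it through.** The point is about an event definition, so the first step is to set the texts side by side.

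1. Rule (Safety and adverse events): an intervention that ceases under the Table 1 criteria is recorded as an adverse event. No item is exempted.
2. Content (Table 1, stop/withhold column, Other row): includes clinical-team decision and refusal.
3. Taken together: a session stopped for either reason is an adverse event, whether or not anything unsafe happened.
4. Other routes (Group 2 section; Discussion): deviations and reasons for non-delivery are recorded separately, so these stops already have a place in the data.

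**Figure cited in the article.** The safety section cites a review in which "1110 patients underwent 5267 rehabilitation sessions" and "physiological abnormalities or potential adverse events occurred in only 6 per 1000 interventions". The event count is not given, so the rate can only be back-calculated: 5267 × 6/1000 = 31.6, or about 32 events. Counts from 29 (5.51 per 1000) to 34 (6.46 per 1000) all round to 6. As described, the numerator names physiological abnormalities and potential adverse events. Whether the review also counted refusals cannot be seen from the article.

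**Illustration of size.** The documents give no rate of refusal or team-decision stops, so the rate r is an assumption. If a share r of sessions is stopped this way and each stop is recorded, the rise in the recorded rate is 1000 × r per 1000 sessions:

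| Assumed r | Rise per 1000 sessions |
|---|---|
| 1% | 10 |
| 2% | 20 |
| 5% | 50 |

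To turn this into counts, take 90 patients randomised 1:1, about 45 in the intervention arm, with two sessions a day on 5 days a week: 45 × 10 = 450 scheduled sessions per week of treatment. Treatment length per patient is also an assumption. One, two or four weeks give 450, 900 or 1800 scheduled sessions, with four weeks matching the 28-day maximum. At r = 2%, the added records are 0.02 × 450 = 9, 0.02 × 900 = 18 and 0.02 × 1800 = 36.

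For scale only, if true safety events occurred at the review's 6 per 1000, the same session numbers would give 0.006 × 450 = 2.7, 0.006 × 900 = 5.4 and 0.006 × 1800 = 10.8. These use all scheduled sessions as the denominator; with fewer sessions started, both sets of counts shrink in proportion.

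**The case against.** Several arguments on the other side carry weight.

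- **Ceasing is not withholding.** The rule speaks of an intervention that ceases, which suggests a session already under way. A refusal beforehand would then be a withheld session and not an adverse event. This may be the intended reading and would reduce the effect, but the shared stop/withhold column leaves it open. Refusals and team decisions during a session are caught either way.
- **One-arm bias.** A reader might infer that only the intervention arm generates these records. The documents do not establish that. The rule covers any intervention, the Table 1 title refers to physical therapy in general, and the safety section says all adverse events are documented. It is true only that Table 1 is applied explicitly to Group 2 alone, which makes the scope ambiguous.
- **Excess over the cited rate.** A reader might divide an assumed 50 per 1000 by the review's 6 and report roughly an eightfold excess. That ratio merely restates the assumed refusal rate. The article uses the review as background and plans no comparison with it, and what the review counted cannot be checked.
- **Double use of one event.** A stop that counts both as non-delivery and as an adverse event is not an error in itself. A fall during a session properly counts as both.
- **No planned analysis is affected.** Adverse events are not among the feasibility or secondary outcomes, and the Statistical analysis section describes no contrast between arms for them. This limits the consequence to descriptive safety reporting and later planning.
- **The data may be separable, and the full protocol may define events.** If the reason for each stop is kept, the two items can be split off afterwards. But the article does not merely leave the definition to another document. It states a rule, and that rule gives the wrong count when followed.

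**Conclusion.** The concern holds in a limited form. The stated rule and the content of Table 1 together make refusal and clinical-team decision adverse events whenever they stop a session. The safety count reported to the committee and used in planning the next trial would therefore not measure safety alone. This conclusion rests on the text and needs no assumption about rates.

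The size cannot be determined from the documents. The 10 to 50 per 1000 sessions shown for 1% to 5% of sessions is an illustration on an assumed rate, and would be smaller if few such stops happen mid-session. No hypothesis test, sample-size figure or feasibility criterion is affected. It is worth correcting because safety is a declared subject of the study and the correction is nearly free.

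**What to change.** Reconcile the safety section with Table 1 for recording purposes only, leaving every clinical criterion for starting, withholding or stopping a session as it stands:

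1. Refusal by the patient or representative, and clinical-team decision, are coded as reasons for non-delivery. They are recorded as adverse events only if an underlying safety event occurred, in which case that event is what is recorded.
2. A session withheld before it starts is not in itself an adverse event.
3. The same recording rule applies in both arms, stated explicitly, since Table 1 is at present tied by name only to Group 2.

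The cost is a sentence or two of text and, if not already present, one reason code on the case report form. Reasons for non-delivery are already collected for protocol interventions. Where the reason for each stop has been kept, records made so far can be recoded. If usual-care physiotherapists do not already note the reason when a session is stopped, point 3 adds a small recording task for them.
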